### Economic evaluation

To help employers and managers to understand the possible financial consequences or benefits of the implementation of PerfectFit@Night, cost-benefit analyses from the employers perspective will be conducted if the intervention has been proven effective. To perform the economic analysis, three measures are included in the study.

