**Methods:**

The study population will consist of healthcare workers, nurses and physicians, with night shifts in a large Dutch academic hospital. The intervention consists of individual and environmental intervention elements: i) an e-learning for healthcare workers to increase knowledge and awareness on a healthy lifestyle during night shifts, ii) a powernap bed to take powernaps during night shifts, iii) the availability of healthy food at the department during night shifts, iv) a workshop on healthy rostering at the level of the department, and v) individual sleep coaching among the high risk group. In a longitudinal prospective study, data will be collected 1 month before the start of the intervention, in the week before the start of the intervention, and three and 6 months after the start of the intervention. The primary outcomes are sleep, fatigue, and need for recovery. The implementation process will be evaluated using the framework of Steckler and Linnan. Cost-benefit analyses from the employers perspective will be conducted to understand the possible financial consequences or benefits of the implementation of PerfectFit@Night.

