**Discussion:**

The feasibility and effectiveness of this workplace health promotion program will be investigated by means of an effect, process and economic evaluation. If proven effective, PerfectFit@Night can be implemented on a larger scale within the healthcare sector.

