#### Primary outcomes

The primary outcome measures are sleep, fatigue, and need for recovery, which are measured at all four time points.

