#### Productivity loss

Productivity costs is measured using costs due to absenteeism (sickness) and due to presenteeism (loss of productivity at work). Absenteeism is measured using three questions regarding the sickness absence of the past month. To measure productivity, two questions of the Productivity and Disease Questionnaire (PRODIQ) are asked [41]. These questions concern the amount of work done during the last work day compared to a general work day (on a scale from 0 to 10), and the reason for not being 100% productive.

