## Conclusion

The PerfectFit@Night intervention aims to improve sleep, fatigue, and recovery of night workers in the healthcare sector by introducing an intervention program which combines universal and indicated prevention targeting both individuals at the workplace as well as the work environment. Both the effectiveness, implementation process, and cost-benefit of the PerfectFit@Night intervention will be evaluated.

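### The cost-benefit analysis depends on an undefined condition of proven effectiveness, which four other places in the article omit and which works against its stated purpose

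*Protocol article*

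**What the plan says.** The operative text is in the Economic evaluation section: "cost-benefit analyses from the employers perspective will be conducted if the intervention has been proven effective". The same sentence gives the purpose, which is to let employers and managers see what the programme may cost them or bring them.

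Elsewhere the condition is absent:

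- Abstract, Methods: "Cost-benefit analyses from the employers perspective will be conducted to understand the possible financial consequences or benefits of the implementation of PerfectFit@Night". The main Discussion repeats this statement.
- Abstract, Discussion: feasibility and effectiveness "will be investigated by means of an effect, process and economic evaluation".
- Conclusion: "Both the effectiveness, implementation process, and cost-benefit of the PerfectFit@Night intervention will be evaluated".

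On what effectiveness means, the Background says that it will be evaluated on sleep, fatigue and recovery, and the Primary outcomes section says: "The primary outcome measures are sleep, fatigue, and need for recovery, which are measured at all four time points". On what generates the financial benefit, the Productivity loss section says: "Productivity costs is measured using costs due to absenteeism (sickness) and due to presenteeism". Neither absenteeism nor presenteeism is listed among the primary or secondary outcomes. The Intervention costs section counts development, implementation and staff labour, and leaves out items already bought, such as the powernap beds.

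**The concern.** There are three linked problems. First, the article states two plans that cannot both be followed when the effect result is negative. Second, the condition cannot be applied as written. There are three primary outcomes and two follow-up times, and no rule says whether one, all or a particular one must succeed, so the rule could be settled after the results are known. Third, the condition is tied to the wrong quantity. Net benefit is productivity gained minus intervention cost, and neither term is a primary outcome. A non-significant result on sleep does not show that productivity was unchanged, and a significant one does not show that the gain covered the cost.

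At stake is the usefulness of the economic result to the employer. Where no effect is shown, the development, implementation and staff costs have still been incurred. That is a financial consequence, and the condition would leave it unreported.

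**Working it through.** **Inputs from the Sample size section.** Power 0.80, significance level 0.05 (sidedness not stated; two-sided assumed), effect size 0.27 in BSWSQ sleep quality, 5 departments of 20, ICC 0.05, equal within- and between-person variance, two measurements before and two after.

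**Assumptions not in the documents.** The gate is a significant result in the favourable direction. The correlation r between the productivity estimate and the gate estimate is 0 to 0.5. Where three outcomes are considered together, their estimates correlate at 0.3 to 0.5.

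**1. The plan's own power.** Design effect = 1 + 19 × 0.05 = 1.95. With total variance 1 and within-person variance 0.5, the variance of (mean of two post − mean of two pre) is 0.5 × (1/2 + 1/2) = 0.5. The standard error is √(0.5 × 1.95 / 100) = 0.0987. Power = Φ(0.27/0.0987 − 1.96) = Φ(0.774) = 0.78. An effect size of 0.277 gives 0.80. The stated power is thus reproduced to within 2 points and is used below.

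**2. How often the analysis would be missing.** For a single gating outcome, P(missing) = 1 − power. Sleep quality is the natural single outcome because it is the only one for which the trial is sized.

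| Gate | Situation | Missing |
|---|---|---|
| Sleep alone | power 0.80 as planned | 20% |
| Sleep alone | power 0.50 (smaller true effect) | 50% |
| Sleep alone | no effect | 97.5% |
| Any of three | each outcome at power 0.80 | about 3–5% |
| Any of three | no effect | about 93–94% |
| All three | each outcome at power 0.80 | about 39–43% |

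The three-outcome rows come from simulation of correlated normal test statistics (400,000 draws). The spread between rows at planned power, from about 3% to 43%, is produced solely by the choice of rule that the article leaves open.

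**3. Selection when the gate is passed.** For one outcome with expected test statistic δ = 1.96 + Φ⁻¹(power), the conditional mean given significance exceeds δ by λ = φ(1.96 − δ)/power. At power 0.80, δ = 2.802 and λ = 0.280/0.80 = 0.35 standard errors, so the gating estimate itself is inflated by 3.152/2.802 = 1.125.

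The productivity estimate moves by r × λ standard errors:

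- r = 0: 0
- r = 0.3: 0.3 × 0.35 = 0.105
- r = 0.5: 0.5 × 0.35 = 0.175, or about 0.18

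At power 0.50, λ is 0.80, and r = 0.5 gives 0.40 standard errors. With three outcomes at power 0.80 each and r = 0.3, the shift is about 0.03–0.04 standard errors under an any-of-three rule and 0.21–0.25 under an all-of-three rule.

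**The case against.** The unconditional statements stand in the abstract, Discussion and Conclusion, while the Economic evaluation section is the operative text. A summary that drops a qualifier is loose wording rather than a rival analysis plan. The condition also has a logic: the abstract links wider implementation to proof of effect, and the economic question matters most where roll-out is in view. It is declared in advance, so a reader can allow for it. These points reduce the weight of the contradiction. They do not define the condition, and they do not answer the mismatch with the stated purpose, which covers costs as well as gains.

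A reader might also infer more than the documents support:

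- That the article gates the analysis on significance for sleep, fatigue or recovery. This is a plausible reading, given how the Background describes effectiveness and the 5% level in the Effect evaluation section, but the Economic evaluation section names neither outcome nor test.
- That the analysis would often be missing. At the planned effect it is missing 20% of the time for sleep alone and about 3–5% for any of three. It becomes frequent only if the true effect is smaller or absent, or if all three outcomes must succeed.
- That the reported net benefit would be biased upwards. The 12.5% inflation applies to the gating outcome. Any shift in productivity depends on a correlation that the documents do not give. It is zero if that correlation is zero, and small at planned power.

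**Conclusion.** The point holds as an undefined condition, inconsistent with four other statements in the article and at odds with the purpose of the analysis. The firmest part needs no arithmetic: net benefit rests on measures that are not primary outcomes, and the costs are incurred whether or not an effect is shown.

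The figures of 20% missing at planned power and 97.5% under no effect rest on the assumption that the gate is a significant favourable result on sleep alone, tested two-sided at 5%. An upward shift of 0 to 0.18 standard errors in the productivity estimate is a possible consequence, not an established one, and rests on assumed correlations of 0 to 0.5. The primary effect analysis is unaffected, so this is a recommended correction to a supporting evaluation.

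**What to change.** Delete the condition in the Economic evaluation section and state that the cost-benefit result will be reported whatever the effect result. Give an interval for net benefit by a method that respects clustering by department and the small number of departments (five in the sample size calculation, at least six planned). Resampling workers alone would ignore the assumed ICC of 0.05, and resampling five or six departments is too few for a dependable interval. The method therefore needs to be chosen with that in mind, for example a mixed model with a small-sample correction.

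If the condition is kept, the minimum is to define it (outcome, time point, test, and any-or-all rule) and to carry it into the abstract, Discussion and Conclusion. That removes the contradiction but not the mismatch with the stated purpose.

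The cost is a little extra analysis, since the cost and productivity measures are already included in the study.

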#### Intervention costs

These costs are related to the development and implementation of the intervention. They also include labor costs of the intervention staff. Some intervention elements, such as the powernap beds, have already been purchased by the departments. Therefore, these elements are not taken into account in the economic evaluation.

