#### E-learning for night workers

To increase knowledge and awareness on working healthy during night shifts, an interactive e-learning is developed for healthcare workers with night shifts. This e-learning focuses on the effects and possible risks of night work, and it proposes additional information and advice on how to decrease these risks. The e-learning consists of three short modules of approximately ten to fifteen minutes each, of which each on a specific topic, namely the impact of night work on health, sleep and powernaps, and nutrition and physical activity. The e-learning concludes with a test for self-assessment. The night workers receive credits (Continuing Medical Education) to motivate them to start and complete the e-learning.

In line with the ASE model, the e-learning targets i) beliefs about, for example, the working mechanisms of powernaps to change attitude, ii) requirements in the social setting (e.g., subjective norms, social support, role models) to change social influence, and iii) challenging night workers to set goals and experiment to enhance self-efficacy.

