#### Coaching among risk group with existing large sleep problems

The previously described intervention elements are mainly focused on universal prevention of risks due to night work. Additionally, night workers with existing large sleep problems and fatigue are offered sessions with a sleep coach to reduce these problems (indicated prevention). Night workers that score low on subjective global sleep quality (assessed using Pittsburgh Sleep Quality Index (PSQI) [24]) and high on fatigue (assessed using the Short Fatigue Questionnaire (SFQ) [25]) at the baseline measurement are offered coaching sessions, online or face-to-face. The coaches provide evidence-based methods, based on cognitive behavioral therapy insomnia (CGTi), to target the individual problems of the night workers. Participants who accept the invitation for coaching sessions are offered 2–3 sessions of 30–40 min, based on the needs of the individual. During these sessions, the coach proposes the relevant topics to be discussed based on the individual needs and issues of the participant. Before the first session, participants are asked to fill out a screening form, a questionnaire regarding cognitions about sleep, and an online sleep journal for 2 weeks. During the first session, the trajectory and goals are discussed and specified. Then, the participants’ biological rhythm is discussed, specifically taking into account the irregular work shifts. Targeted information and tips about the irregular rhythm and sleep in general are also given by the coach. During the second session, the previous exercises are discussed. Thereafter, practical tips regarding lifestyle, sleeping behavior, and relaxation are given. It is also evaluated whether a third session is needed. During the third session, exercises that need follow-up are discussed, as well as applications of the techniques in the future.

The intervention will be implemented throughout a period of 3 months, and thereafter may continue at the discretion of participating individuals and departments within the hospital.

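### The intervention cost pools development with implementation and leaves out the powernap beds, so the net benefit does not isolate what implementing the programme costs an employer

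*Protocol article*

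**What the plan says.** The Economic evaluation section gives the purpose: "To help employers and managers to understand the possible financial consequences or benefits of the implementation of PerfectFit@Night". It fixes perspective and condition: "cost-benefit analyses from the employers perspective will be conducted if the intervention has been proven effective". The abstract's Discussion paragraph names the later decision, saying that if effective, "PerfectFit@Night can be implemented on a larger scale within the healthcare sector".

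The Intervention costs paragraph then sets the scope: "These costs are related to the development and implementation of the intervention". It adds one labour item, "They also include labor costs of the intervention staff", and makes one exclusion: "Some intervention elements, such as the powernap beds, have already been purchased by the departments". The paragraph concludes that elements bought in this way stay out of the economic evaluation.

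Three other places bear on this. The Powernaps section says the participating departments or the hospital pay for the beds. The Workshop on healthy rostering section says the workshop is adapted to each department. Strengths and limitations lists dependence on department heads' willingness to invest in beds and healthy food as a limitation.

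**The concern.** The question concerns implementation, but the cost definition mixes implementation with development and removes a core item of implementation. Developing the programme (the Methods describe a needs assessment, and the e-learning is described as developed) is mostly not repeated by a department or hospital that takes up the finished product. Beds are different: each adopting department needs one, and the protocol treats paying for it as a real hurdle.

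The paragraph also treats past spending unevenly. Beds go out because the money is already spent. Development stays in, although most of it must also have been spent before the programme could start.

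At stake is whether an employer can use the reported net benefit. A manager deciding on adoption would read a figure that carries costs they would not face and lacks a purchase they would have to make.

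**Working it through.** The plan states no cost, wage or net-benefit figure, so there is nothing to reproduce. The check is whether any consistent costing rule gives the stated scope, and then which way the scope moves the result.

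**Step 1: test the scope against possible rules.**

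| Rule | Development | Beds |
|---|---|---|
| Ignore money already spent | out (for the part already spent) | out |
| Count all project spending | in | in |
| Count what an adopting employer pays | largely out | in |
| **Intervention costs paragraph** | **in** | **out** |

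The stated scope matches none of the three rules. It is close to the reverse of the third, which is the rule that fits the stated purpose and the foreseen roll-out. A fourth rule, counting only what the research project itself paid, could give the stated scope if the project funded development. But the documents do not say who funded it, and that rule is not the employer's perspective, because the departments and hospital that pay for the beds are the employer.

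**Step 2: direction of the effect.** Let *D1* be one-off development, *D2* development that recurs for each adopter (such as tailoring the workshop), *I* the other implementation costs, *B* the cost of the beds and *G* the gains.

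- Plan: net benefit = *G* − (*D1* + *D2* + *I*)
- Adopting employer: net benefit = *G* − (*D2* + *I* + *B*)
- Plan minus adopter = *B* − *D1*

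The plan understates the adopter's net benefit if one-off development cost more than the beds, and overstates it if it cost less. With neither amount given, the sign stays open. Any other element dropped as already bought would add to *B*; the text gives the beds only as an example.

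**Step 3: participants' time, as a clarification only.** The paragraph does not say whether this time counts. Its scale follows from stated durations:

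- E-learning ("The e-learning consists of three short modules of approximately ten to fifteen minutes each"): 3 × 10 to 3 × 15 = 30 to 45 min per worker.
- Coaching, 2–3 sessions of 30–40 min: 2 × 30 to 3 × 40 = 60 to 120 min per coached worker.
- Scaling number: the Sample size section's 204 night workers, which reproduces as 100 / (0.70 × 0.70) = 204.1.
- E-learning if all 204 complete it: 204 × 30/60 = 102 h to 204 × 45/60 = 153 h.
- Coaching, with an assumed 10% to 30% coached: 204 × 0.10 × 1 h = 20.4 h to 204 × 0.30 × 2 h = 122.4 h.
- Together: about 122 to 275 h. Workshop time cannot be added, since no duration is given.

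These hours are a cost to the employer only where they fall in paid working time, which the documents do not state.

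**The case against.** Several points can fairly be made for the plan. The documents do not say who paid for development; if the hospital did, it is a real cost to that employer. Not all development is one-off, since the rostering workshop is adapted to each department. The analysis is conditional and secondary, and cost lines can still be split when it is run. These points stand, and they limit the conclusion to a mismatch of scope with low severity. They do not remove it: even for this hospital as employer, a total-cost view that keeps development would also keep the beds.

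That the article is condensed is a weaker defence here, because the pooling and the exclusion are both stated.

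A reader might go further and infer that the paid time of night workers and roster makers has been left out. The text does not support that. The labour sentence adds intervention staff to the costs without limiting labour to them, and implementation costs can cover participants' time. Nothing says that the e-learning or coaching takes place in paid hours: the e-learning earns education credits, and for coaching the article says only "Participants who accept the invitation for coaching sessions are offered" two to three sessions, online or face-to-face. An itemised cost list is also something an article commonly leaves to the full plan.

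A reader might also conclude that development is overstated by some fixed factor, or that the sign of the net benefit is meaningless. Either claim would need amounts for development, beds, wages or gains, and the documents give none.

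**Conclusion.** The point holds as a mismatch between the stated cost scope and the stated question. Development is pooled with implementation, and an employer-paid core element is excluded, so the net benefit will not isolate the cost of implementing the programme. The bias equals bed cost minus one-off development cost, and neither its size nor its sign can be found from the documents.

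This rests on two readings: that the result is meant for employers considering adoption, as the Economic evaluation section and the abstract indicate, and that most development work would not be repeated. The treatment of participants' time is an open question and not a shown error. Severity is minor, because the primary outcomes and the mixed-model analyses do not depend on this definition.

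**What to change.** In the Intervention costs paragraph:

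- Define the base-case intervention cost as what an adopting employer pays to implement the programme. Include purchased elements such as the beds, at purchase or annualised cost, and any department-specific tailoring that recurs.
- Report development cost on a separate line, and show total project spend beside the base case as a scenario.
- State whether participation in paid working time is counted. Where it is, estimate the hours from the participation, completion and usage records named under Process evaluation, multiplied by the nominal module and session lengths. Those records are given as counts, not hours, so the workshop's duration and whether the time was paid would have to be noted as well.

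The cost is a rewritten paragraph, a split cost sheet, the bed purchase prices and those few extra notes. The downside is that the base case no longer equals total project spend, which is why that total should stand beside it.

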### Intervention elements

Based on the needs assessment and program objectives, the intervention consists of the following individual and environmental elements (see Fig. 1): i) an e-learning for night workers to increase knowledge and awareness on a healthy lifestyle during night shifts, ii) a powernap bed to take powernaps during night shifts, iii) the availability of healthy food/snacks at the department during night shifts, iv) a workshop on healthy rostering at the level of the department (for roster makers), and v) individual sleep coaching among the high risk group.

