#### Powernaps

In order to accept and encourage healthcare workers to take a nap during night shifts, powernap beds were purchased. Following the ANGELO framework, installing a powernap bed at the department, which is placed in a quiet and suitable room (i.e., physical factor), is paid by the participating departments or hospital (i.e., economic factor), and it is allowed by the management to take a powernap (i.e., political and cultural factor). At the individual level, sociocultural factors are role models, social support from colleagues and the management, and social norms regarding powernaps. It is known that attitude towards and acceptance of taking naps during night shifts is challenging. Therefore, the e-learning provides information about the working mechanisms of powernaps and encourages the intention to use powernaps. Besides, examples of good practices in other departments and hospitals are given, and workers of the department are involved as ambassadors (role models).

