#### Availability of healthy nutrition at work

To encourage healthy nutrition, healthcare workers with night shifts should have insight in healthy nutrition, and healthy food needs to be offered by the employer. The night workers are informed about the best timing to consume specific nutritional elements through the e-learning module, but also by flyers and a webinar. This information is established in a collaboration with a dietician who specializes in chrono nutrition, based on the latest insights from research and experiences. Following the ANGELO-framework, healthy food is made available during night shifts by providing products (i.e., physical factor) that is paid by the department (i.e., financial factor). The heads of the departments agreed to provide and pay for the food (i.e., political factor). At the individual level, sociocultural factors that are a condition for change in diet to occur are role models (ambassadors), social support from colleagues and the management, and social norms.

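### The employer-perspective cost-benefit analysis gives zero cost to powernap beds that the employer paid for, while the effect of napping stays on the benefit side

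*Protocol article*

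**What the plan says.** The Economic evaluation section of the protocol article sets the perspective and a condition: "cost-benefit analyses from the employers perspective will be conducted if the intervention has been proven effective". Its purpose is "To help employers and managers to understand the possible financial consequences or benefits of the implementation of PerfectFit@Night".

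The Intervention costs section then defines what is counted: "These costs are related to the development and implementation of the intervention", with the labour of intervention staff included. An exception follows: "Some intervention elements, such as the powernap beds, have already been purchased by the departments". The consequence drawn is "Therefore, these elements are not taken into account in the economic evaluation".

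Elsewhere, the Intervention elements section lists "a powernap bed to take powernaps during night shifts" as the second of five elements. The Powernaps section says the beds were bought to encourage napping on night shifts, and that the bed "is paid by the participating departments or hospital (i.e., economic factor"). On the benefit side, the Productivity loss section uses absenteeism and presenteeism. The Strengths and limitations section says that effects cannot be attributed to single elements, and it describes beds and food as things department heads must be willing to invest in.

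**The concern.** From an employer's perspective, payment by the employer is the reason a cost belongs in the analysis. Here it is given as the reason to leave the cost out. The participating departments are part of the hospital, so a bed bought by a department is an employer outlay, and it was made for an element of the programme under evaluation.

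Costs and benefits also no longer match. The productivity outcome reflects the whole package, including any effect of napping in the beds. Because the article says element effects cannot be separated, the benefit due to the beds cannot be taken out to match the cost that was taken out.

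At stake is the figure given to employers and managers who are deciding whether to implement the programme. An employer that does not own beds would read a net benefit that leaves out a purchase it has to make.

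**Working it through.** **No figure to reproduce.** The article gives no bed price, programme cost, net benefit or benefit-cost ratio. The direction follows from algebra. The size can only be shown under stated assumptions.

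**Direction.** Let B be the measured benefit, C the counted cost and X > 0 the omitted bed cost.

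- Reported net benefit: B − C. Full net benefit: B − C − X. Difference: (B − C) − (B − C − X) = X.
- Reported ratio: B/C. Full ratio: B/(C + X). For B > 0 the reported ratio is too high by the factor (C + X)/C = 1/(1 − s), where s = X/(C + X) is the bed share of full cost.
- For illustration only: s = 0.10 gives 1/0.90 = 1.11; s = 0.25 gives 1/0.75 = 1.33; s = 0.50 gives 1/0.50 = 2.00. The article does not say what s is.

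**Workers per bed.** The Sample size section gives 100 participants in five departments, 70% initial participation, 30% loss to follow-up, and 204 night workers needed at baseline.

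- Check: 100/(0.70 × 0.70) = 204.1, which agrees with 204. The average cluster of 20 is therefore the number analysed per department, after non-participation and loss. It is not the number of night workers who could use the bed.
- Night workers per department: 204/5 = 40.8, about 41.

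**Omitted cost per worker.** Assumptions not in the article: EUR 1,000 to 10,000 per bed, one bed per department, and a useful life of five years with no discounting.

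| Assumed bed price | Per worker (price/40.8) | Per worker-year (÷ 5) |
|---|---|---|
| EUR 1,000 | EUR 24.5 | EUR 4.9 |
| EUR 10,000 | EUR 245 | EUR 49 |

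The Study population section speaks of at least six departments. Spreading 204 over six gives 204/6 = 34 per department, hence EUR 29 to 294 per worker (1,000/34; 10,000/34). The order of magnitude is the same. Larger departments, which the Sample size section allows for, would lower the figures; more than one bed per department would raise them.

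**The case against.** The strongest defence is that the purchase is sunk. The article says that after three months the intervention may continue at the discretion of the participating individuals and departments (end of the sleep-coaching section). For a department that already owns a bed, its price has no bearing on whether to continue. This stands for that narrow decision. It does not serve the stated purpose, which is to inform employers about implementing the programme, or the larger-scale implementation foreseen in the Abstract.

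The exclusion is also stated openly with its reason, so a reader could add a bed price, and no trial data would be lost. That bears on severity and does not justify the base case.

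Two stronger readings are tempting, but the article does not support them.

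- **That food is excluded too.** The phrase introducing the beds leaves the list open, and the article says "healthy food is made available during night shifts by providing products (i.e., physical factor) that is paid by the department (i.e., financial factor"). But the exclusion covers things already bought, whereas food is a continuing provision that department heads agreed to pay for. Nothing says it is left out, so this warrants only a request for confirmation.
- **That the whole analysis must favour the programme.** The bed exclusion on its own does so. But counted costs include development, which is at least partly one-off and which a later adopter need not pay again. That works in the opposite direction for roll-out, and the net direction for such an employer cannot be worked out from the article.

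**Conclusion.** The point holds for the beds. The stated rule conflicts with the stated perspective and purpose. Taken alone, it overstates net benefit by exactly the omitted bed cost. The direction of that single effect is certain; its size is not known. The range of about EUR 25 to 245 per worker, or EUR 5 to 49 per worker-year, rests on an assumed price, one bed per department, 41 workers per department and straight-line spreading over five years.

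A reader might infer that a loss-making programme would be shown as cost-saving. That is possible, but with no benefit or total cost in the article it cannot be shown.

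Severity: should fix. The cost-benefit analysis is secondary and runs only if the intervention proves effective. The primary outcomes, the effect models and the sample size are untouched.

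**What to change.** Replace the last sentence of the Intervention costs section so that:

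1. the base case counts the employer-paid beds at purchase price, annuitised over a stated useful life;
2. any element still excluded is named with its reason, and the text confirms that department-paid food is counted;
3. the result without already purchased beds appears only as a sensitivity analysis, labelled as applying to departments that already own them.

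No new line is needed for intervention staff labour, which the section already includes.

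The cost is small: bed purchase records must be obtained from the departments, one annuitised cost line and one sensitivity run added, and food spending collected if it is not already recorded. Net benefit will look slightly less favourable. No participant data, design feature or sample size changes.
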